#### Inclusion criteria

Included participants will be aged 60–85 years at baseline and have a memory complaint which worries them. Thus, they will answer ‘Yes’ to both of the following questions: “Do you feel like your memory is becoming worse?” and “Does this worry you?” [20, 21]. They will also have minimal or no cognitive deficit. Specifically, they will have: (1) a delayed recall score on Story A of the Logical Memory subtest of the Wechsler Memory Scale—Revised [33] above the ADNI education-adjusted cutoffs [34] (≥ 9 for 16+ years of education; ≥ 5 for 8–15 years of education; ≥ 3 for 0–7 years of education); (2) a Montreal Cognitive Assessment (MoCA) total score above 20; (3) a delayed recall score on the CERAD word list above 4; and (4) a global Clinical Dementia Rating (CDR) score lower than 1.0. Based on these criteria, the individuals recruited in the study will meet criteria for SCD or early MCI [20, 21, 35].

Additional inclusion criteria are sufficient visual and auditory acuity, sufficient English/French proficiency to undergo assessment and participate in the intervention, the ability to commit for the whole intervention and follow-up assessments, having an internet connection at home, and an informant to provide corroborative information.

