### Baseline characterization

Different measures will be used at baseline for diagnosis and clinical characterization and for measuring outcomes. Participants will be characterized on a number of psychological, cognitive, and physical variables, as well as past and current lifestyle and activities (please refer to ClinicalTrials.gov NCT03402919 and to Additional file 2: Appendix 1 for a description of the baseline assessments). This will include information on demographics (age, sex, education), occupations and hobbies, social engagement, general health, current and past medication, medical history, family medical history, physical measurements (weight, blood pressure, etc.), neurological examination, blood, saliva and urine collection (and an optional lumbar puncture), screening tests for mild cognitive impairment or dementia, gait evaluation, sensory processing (visual and auditory acuity), smoking and alcohol use, nutritional habits (Canadian Longitudinal Study on Aging (CLSA) Short Diet Questionnaire [43], and abbreviated version of the SCREEN II [44]), physical exercise (Physical Activity Scale for the Elderly (PASE) [45] and California Teachers Study Long Term Recreational Physical Activity Survey [46]), self-perception and psychological state (self-administered questionnaires, including Beck Depression Inventory II (BDI-II) [47] and Beck Anxiety Inventory (BAI) [48]). Biosamples will allow investigation of genetic biomarkers of a high risk of Alzheimer’s disease and of brain plasticity (apolipoprotein (Apo)E4, brain-derived neurotrophic factor (BDNF), and catechol-O-methyltransferase (COMT)). Cognitive reserve proxies will be evaluated using years of education and a modified version of Rami and colleagues cognitive reserve questionnaire adapted for French and English by the CIMA-Q team [32, 49]. As the intervention involves training participants on videogames and music and/or second language learning, the participants prior experience in those areas will be characterized through questionnaires of game literacy (Game Experience Questionnaire, created by our team), computer proficiency (Computer Proficiency Questionnaire (CPQ) [29]), experience with music (Music Experience Questionnaire, created by our team), and multilingualism (Language Experience and Proficiency Questionnaire (LEAP) [50]).

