#### Analysis of moderators

A small set of time-invariant variables will be included as predictors to assess their effects on primary and secondary outcomes. Three pre-specified subgroup analyses will be done according to sex (male versus female), education (less versus more than 12 years), and age (younger versus older than 75 years at baseline). Other subgroup analyses will be exploratory, such as reserve score based on the adapted version of the Rami and colleagues cognitive reserve questionnaire [32, 49], genetic markers of brain plasticity and risks for dementia (APOe4, BDNF, and COMT), baseline brain structure and function, depression (BDI-II [47]), and anxiety (BAI [48]). We will also include the expectations of participants regarding the cognitive training, compliance with the intervention (percentage of sessions attended and percentage of homework completed), amount of knowledge acquired during the intervention, and self-efficacy perception (personality measures). Stepwise regression analyses with the per-protocol participants from the cognitive training group will be used to explore whether the moderators predict delayed memory change scores at the two follow-up time points.

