This study has many strengths. One of them is the inclusion of an active control condition and strategies used to reduce and control for the expectation effects of participants. The majority of intervention studies use a no-contact or wait-list control group comparison, a design that does not allow control for the effects of social stimulation, expectations, or additional stimulation from everyday routine. By including an active control condition that mirrors the structure and the level of social engagement of the intervention condition, while providing the same expectations in terms of potential benefits, this study is in a better position to confidently attribute any positive results to the content of the program. This study will also measure generalization of cognitive benefits to everyday tasks, which is an important indication of the impact of the intervention. Furthermore, the study includes a number of approaches to increase transfer to activities of daily living, for instance practicing the cognitive strategies during the leisure sessions and including homework for practice in the home environment of participants. It will also measure the neural substrates of training-related benefits by using MRI and fMRI, which will contribute to building knowledge on the brain mechanisms by which such interventions exert their effects. Finally, few studies have assessed the long-term effect of cognitive interventions up to more than a year after training and, thus, the 24-month assessment included here will provide critical information on the maintenance of the effects as well as their impact on cognitive decline.

An important component of this study is to enroll participants with limited education to compare training efficacy as a function of cognitive reserve proxies. This is critical because cognitively stimulating interventions might be particularly beneficial to those individuals who are at greater risk of developing dementia. Furthermore, results will be more representative of the general population and hence more generalizable. Finally, as the population will be well characterized, it will be possible to assess whether some genetic, cognitive, or demographic characteristics are associated with a better response to treatment. This will allow provision of recommendations for the type of older adult who is most likely to benefit from such intervention.

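### The education and age subgroups leave exactly 12 years and age 75 unassigned, and the only fully defined between-arm moderator tests split two numeric variables in two

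*Protocol article*

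**What the plan says.** The Analysis of moderators section gives the subgroup tests a formal status: "Three pre-specified subgroup analyses will be done according to sex (male versus female" is followed directly by "education (less versus more than 12 years), and age (younger versus older than 75 years at baseline". No other section says where a value lying on either cut-point goes.

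Both boundary values can occur. The Inclusion criteria section admits people "aged 60–85 years at baseline" and sets no limit on schooling. Its memory-score cut-offs use whole-year education bands that meet without a gap: 16 or more years, then "≥ 5 for 8–15 years of education; ≥ 3 for 0–7 years of education". Education is held as a number, since "Cognitive reserve proxies will be evaluated using years of education", and age is collected at baseline.

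Two other sentences in the moderator section bear on the point. One says that a few characteristics that do not change over time will enter as predictors, without giving their form. The other describes a stepwise regression restricted to per-protocol participants of the training arm.

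**The concern.** A pre-specified subgroup should place every participant. Here the cut-points are fixed but the side that takes the cut-point value is not. If nothing else settles it, someone has to choose once data exist, and that is the freedom pre-specification is meant to remove.

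The second issue matters more. The objectives include a hypothesis that sex, age and education modify the effect, and the Discussion says: "An important component of this study is to enroll participants with limited education to compare training efficacy as a function of cognitive reserve proxies". The article's between-arm route to an answer for age and education is a two-level split of a variable measured in years. Such a split treats a 61-year-old and a 74-year-old as alike, and a 74-year-old and a 76-year-old as different. If the effect changes steadily with age or schooling, much of the information about that change is lost, in an analysis that has little to spare.

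**Working it through.** The article states no figure that depends on these definitions, so there is none to reproduce. The check has three parts.

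**1. Do the categories cover the eligible range?** For education in whole years, below 12 and above 12 together omit 12. For age in completed years, below 75 and above 75 together omit 75, which lies inside 60–85. With decimal age the omitted set is a single point and is practically empty. With whole-year education the gap is real.

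**2. How many people might be affected?** Input from the document: N = 144. The shares are assumptions.

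- Exactly 12 years: a smooth (rounded normal) distribution with mean 14–15 and SD 3–3.5 years gives 8–11%. Schooling may cluster at certificate years, so the wider range 5–25% is used: 144 × 0.05 = 7 to 144 × 0.25 = 36 people.
- Age 75, uniform over the 26 whole-year ages 60–85: 1/26 = 3.8%, or 144/26 = 5.5 people. Normal with mean 71 and SD 5.5: 5.7%, or 8.2 people.
- Absent from at least one of the two analyses, assuming independence and the uniform age share: 144 × [1 − 0.95 × (25/26)] = 12 to 144 × [1 − 0.75 × (25/26)] = 40.

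**3. How much information does a split keep?** For a moderator whose effect is linear, the share kept is about the squared correlation r² between the numeric variable and its two-level version, with the boundary value assigned to a side.

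- Normal moderator with a fraction p on one side of the cut: r² = φ(z_p)² / [p(1 − p)]. At p = 0.5: 0.399²/0.25 = 0.64. At p = 0.2: 0.280²/0.16 = 0.49. The three assumed education distributions (mean/SD 14/3, 15/3 and 14.5/3.5), split at 12 or fewer, give 0.59, 0.50 and 0.57, inside that range.
- Age uniform over 60–85, split at 75 or older: p = 11/26, group means 80 and 67, variance (26² − 1)/12 = 56.25. So r² = (11/26)(15/26) × 13²/56.25 = 0.73.
- Age roughly normal, truncated to 60–85: mean 71, SD 5.5 gives 0.58; mean 72, SD 6 gives 0.61; mean 70, SD 5 gives 0.47.

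The resulting ranges are about 50–65% for education and 47–73% for age.

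**Context: power for a subgroup contrast.** Inputs from the document: N = 144, 18% attrition, 2:1 allocation, two-sided 0.05. Completers: 144 × 0.82 = 118, that is 39.4 control and 78.7 intervention. For a between-subgroup difference in effect of 0.5 SD of change (an assumption) and a share s in one subgroup, SE = √[(1/39.4 + 1/78.7)(1/s + 1/(1 − s))].

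- s = 0.50: SE = 0.390, power = Φ(0.5/0.390 − 1.96) = 0.25.
- s = 0.25: SE = 0.451, power = Φ(0.5/0.451 − 1.96) = 0.20.

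**The case against.** The strongest reply is that the wording is ordinary shorthand for a cut-point in a condensed article. Nothing says that boundary participants will be excluded, and the full protocol or analysis plan may settle the side. That largely stands: on its own, the gap deserves a one-line clarification.

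A reader might infer more, and the documents do not support it. One inference is that boundary participants drop out of two of the three subgroup analyses. In fact someone with 12 years is unplaced only for education and a 75-year-old only for age; losing both needs both values. Another is that the loss falls on the low-education participants whom the trial works to recruit. The article's lower group is below 12 years, and the literal rule removes nobody from it. People with exactly 12 years count as lost from the low end only if one first adopts a category of 12 or fewer, which the article never defines.

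It can also be said that two-level subgroups are conventional, easy to read and limit analytic flexibility, and that the information loss presumes linearity. Both are fair, and they are reasons to keep the subgroups as displays. The sentence about predictors leaves room for numeric terms but does not specify them. The stepwise regression cannot fill the gap: it uses one arm only, so it cannot show whether the difference between arms varies with the moderator.

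**Conclusion.** The point holds as a minor one. Read literally, the two splits do not place everyone, and the only between-arm moderator tests that the article fully defines for education and age reduce numeric variables to two levels. The second part carries the weight, because a better method is available from data already collected.

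The counts (about 5–25% at exactly 12 years, about 4–6% aged 75) rest wholly on assumed distributions, and targeted recruitment of people with less schooling could shift the education figures. The age figure nearly vanishes if decimal age is used. The information figures hold for an approximately linear moderator, which nothing in the documents establishes. With power of only about 0.20–0.25 for a 0.5 SD subgroup difference, continuous modelling improves these tests but cannot be expected to make them strong.

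It would go too far to read this as a threat to the trial's main conclusion. Moderation is a secondary objective; the primary comparison and the 144 participants do not depend on it.

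**What to change.** Before the 4-month data are examined, amend the moderator section in two ways.

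- Make the formal between-arm tests intervention × time × years of education and intervention × time × age, with both moderators continuous, in the mixed model already planned. Sex stays as it is.
- Keep the education and age subgroups as descriptive displays and state which side takes 12 years and which takes age 75, for example 12 or fewer against more than 12, and under 75 against 75 or older. Say whether age is in completed years or decimal.

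The cost is a few lines of text and no new data. The continuous terms assume an approximately linear relation; the subgroup displays serve as the check on that.

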### Dissemination of study data

Data will be presented in international conferences and through publications in journals with peer-reviewed committees (see dissemination plan in Additional file 2: Appendix 3). Study results will also be presented to the public through lay-audience talks and press releases.

## Discussion

The ENGAGE study is a randomized, controlled, double-blind comprehensive cohort design trial to assess the efficacy and the long-term effect of a leisure-based training program in older adults with a memory complaint. The program is multifaceted and combines stimulating leisure activities with strategy-based cognitive training focusing on memory and attention. The overarching objective of the study is to provide empirical support that participation in cognitively engaging activities later in life can promote cognitive health, reduce cognitive decline, and build cognitive reserve.

While there have been a few studies that have shown the efficacy of cognitive interventions for persons with MCI, there has been a limited number of studies that have designed interventions for individuals with SCD or early MCI. However, SCD and early MCI have been suggested to represent a very early stage of future cognitive decline in some individuals, which also means that it is a period where the brain may have its greatest potential for plasticity effects. This makes SCD and early MCI a key phase for cognitive engagement and learning of strategies for memory and attention optimization.

This study has many strengths. One of them is the inclusion of an active control condition and strategies used to reduce and control for the expectation effects of participants. The majority of intervention studies use a no-contact or wait-list control group comparison, a design that does not allow control for the effects of social stimulation, expectations, or additional stimulation from everyday routine. By including an active control condition that mirrors the structure and the level of social engagement of the intervention condition, while providing the same expectations in terms of potential benefits, this study is in a better position to confidently attribute any positive results to the content of the program. This study will also measure generalization of cognitive benefits to everyday tasks, which is an important indication of the impact of the intervention. Furthermore, the study includes a number of approaches to increase transfer to activities of daily living, for instance practicing the cognitive strategies during the leisure sessions and including homework for practice in the home environment of participants. It will also measure the neural substrates of training-related benefits by using MRI and fMRI, which will contribute to building knowledge on the brain mechanisms by which such interventions exert their effects. Finally, few studies have assessed the long-term effect of cognitive interventions up to more than a year after training and, thus, the 24-month assessment included here will provide critical information on the maintenance of the effects as well as their impact on cognitive decline.

An important component of this study is to enroll participants with limited education to compare training efficacy as a function of cognitive reserve proxies. This is critical because cognitively stimulating interventions might be particularly beneficial to those individuals who are at greater risk of developing dementia. Furthermore, results will be more representative of the general population and hence more generalizable. Finally, as the population will be well characterized, it will be possible to assess whether some genetic, cognitive, or demographic characteristics are associated with a better response to treatment. This will allow provision of recommendations for the type of older adult who is most likely to benefit from such intervention.

In spite of these strengths, the study has some potential limitations. Although it offers several leisure activities, and the possibility of excluding one of them should increase motivation and engagement of participants, there is still the possibility that they will find neither music nor Spanish training appealing. This may potentially affect their engagement throughout the program and reduce generalization to real life, where people choose activities they enjoy from among a much larger number of options. Secondly, the training is relatively long, the inclusion of homework will increase burden, and the schedule is demanding. This might have an effect on recruitment success and on attrition rate. Sample size estimation was based on attrition from prior studies but those were different, and it is possible that attrition will be different in the present case. Third, although leisure activities were included to make the intervention appealing, cognitive training sessions may be tedious and increase withdrawal. Finally, while proficiency in Spanish is an exclusion criterion, it was not feasible to have bilingualism as an exclusion criterion because Canada is a bilingual country and Toronto and Montreal have culturally diverse populations. This is of some concern because there is substantial evidence that bilingualism may have a protective effect against dementia (e.g., [15, 70]) and thus bilingualism has the potential to be a confounding variable. However, it will be possible to use bilingualism as a confounding and moderating factor in the analyses if it is found to differ among groups and/or correlate with efficacy.

In conclusion, the purpose of the ENGAGE study is to provide evidence for the short-term efficacy and long-term maintenance of a leisure-based cognitive intervention. Additionally, ENGAGE will provide data regarding the impact of cognitively engaging activities on brain structure and function, as well as providing data on what characterizes good responders to intervention. The ENGAGE study targets individuals with a memory complaint who are at risk of developing AD. Positive results from this study will have major implications for the well-being and health of these individuals by encouraging them to participate in meaningful activities and by providing models for designing impactful interventions that can be used broadly in the community.

## Trial status

Protocol version number V2, December 2018. Recruitment began in September 2017. Date of recruitment completion is anticipated to be March 2020.
